### Total Blood Loss

Approximately 145 mL whole blood will be drawn in patients receiving cisplatin treatment and approximately 55 ml whole blood will be drawn in control subjects (healthy volunteers and cancer control patients).

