## **3. STUDY DESIGN**

This is a prospective, non-randomised, longitudinal, case control study. Patients with cancer who are scheduled to receive high dose cisplatin as part of their standard of care treatment (e.g. non-small cell lung cancer, head & neck cancer) will be enrolled in this study. Control patients with similar cancers who have not had recent major surgery or treatment with nephrotoxic drugs will be enrolled as a control patient population. A cohort of healthy subjects will be enrolled as a separate healthy control population.

Subjects will have a screening assessment where their diagnosis and eligibility for enrolment is confirmed. The study will be explained to them and subjects willing to participate will be asked to give informed consent. Unless documented by clinical

chemistry laboratory results in the previous month, subjects will have a blood sample taken for BUN and serum creatinine to document baseline renal function and confirm they meet the criteria for the study. Eligible patients scheduled to receive cisplatin will have blood and urine samples taken pre-dose on the day of first cisplatin administration and at intervals over the next 3 weeks. Control subjects (cancer patients and healthy volunteers) will attend the clinic to give blood and urine samples at two visits that are 2 days (+/- 1 day) apart.

Enrolled subjects will have blood and urine samples collected for novel biomarkers at the following time-points:

Cisplatin-treated group:

- Pre-dose on day of 1st cycle cisplatin chemotherapy administration (baseline)
- Prior to leaving the clinic following cisplatin administration (or at approximately 8 - 12 hours post-dose for in-patients)
- 24 hours post-dose
- 2 days post-dose
- 4 days (+/- 1 day) post-dose
- 7 days (+/- 1 day) post-dose
- 14 days (+/- 3 days) post-dose
- 21 days (+/- 7 days) post-dose

Control groups (cancer patients and healthy volunteers):

- Visit 1 (within 3 weeks of Screening: this may be the Screening visit after subjects have given their informed consent. In this case, for those subjects who are subsequently found not to qualify for inclusion after lab results are available, stored samples will be discarded and not included in any analysis. Any subjects not included after Screening will not count towards the number of enrolled subjects for the relevant cohort even if samples are taken and later discarded.)
- Visit 2 (2 days [+/- 1 day] after Visit 1)

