**Table 3: Schedule of Activities for healthy control group**

| Healthy control group n=20                        | Screening  | Visit 1  | Visit 2
(2 days post V1) | Visit 3
(14 to 28 d post V1) |
|---------------------------------------------------|------------------------|----------------------|-----------------------------|---------------------------------|
| Informed consent                                  | x                      |                      |                             |                                 |
| Blood sample (5 mL) for clinical chemistry        | x                      | x                    | X                           | x                               |
| Urine sample (10 mL) for urinalysis               | x                      | x                    | X                           | x                               |
| Check subject eligibility                         | x                      |                      |                             |                                 |
| Review adverse events and concomitant medications | x                      | x                    | X                           | x                               |
| Enrol subject                                     |                        | x                    |                             |                                 |
| Blood sample (10 mL) for serum        |                        | x                    | X                           | x                               |
| Blood sample (10 mL EDTA) for plasma              |                        | x                    | X                           | x                               |
| Urine sample (40 mL)                  |                        | x                    | X                           | x                               |

To analyse for DIKI biomarkers as listed in Table 3.

These visits may be combined if subject gives informed consent

This is an observational study. All patients in this study will receive treatment as per standard of care for their conditions. Patients in this study that develop BUN or serum creatinine changes following cisplatin treatment that qualify as acute kidney injury will be managed according to standard hospital treatment protocols.

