### **Control groups**

Control subjects (non-cisplatin treated cancer patients, healthy volunteers) will have blood and urine samples collected as described below. Note that for cancer control group patients who are receiving inpatient treatment, morning blood and urine will be collected in the hospital or clinic they are being treated in. Details of samples collected are given in Section 7.

Blood samples and a urine sample will be collected when subjects arrive in the clinic. If a subject is unable to produce a urine specimen on arrival at the clinic, he/she should be given some fluids to drink in order to produce the sample. As far as possible, clinic visits should be in the morning and should be arranged such that they are within a 2 hour window that is convenient for the patient and clinic staff.

Samples should be provided on:

- Visit 1: this should be within 3 weeks of the Screening assessment (see previous regarding combining Screening and Visit 1).
- Visit 2: this should 2 days (+/- 1 day) after Visit 1.

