|---------------------------|--------------------|--------------------------|----------------|-------------------|----------------|
|                           |                    | Cisplatin group          | Control groups | Cisplatin group   | Control groups |
| Routine laboratory test   | 5                  | 9                        | 3              | 45                | 15             |
| DIKI serum sample         | 10                 | 8                        | 2              | 80                | 20             |
| DIKI EDTA blood           | 10                 | 2                        | 2              | 20                | 20             |
| Total blood volume | -                  | -                        | -              | 145        | 55      |
| Routine urinalysis        | 10                 | 9                        | 3              | 90                | 30             |
| DIKI urine sample         | 40                 | 8                        | 2              | 320               | 80             |
| Total urine volume | -                  | -                        | -              | 410        | 110     |

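### Healthy controls have a third sampling visit in their schedule table but only two in the text, so the stated 55 mL blood and 110 mL urine do not match that table (up to 80 mL and 160 mL)

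*Protocol*

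**What the plan says.** **Schedule table.** Table 3 in Section 3 (schedule of activities for healthy controls, n=20) has four columns: Screening, Visit 1, Visit 2 and a Visit 3 timed at "14 to 28 d post V1". Routine chemistry, urinalysis, serum, EDTA plasma and the 40 mL urine sample are all marked at Visit 3. Table 2, for cancer controls, has no such column.

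**Text.** The Section 3 design text says that control subjects, naming both cancer patients and healthy volunteers, "will attend the clinic to give blood and urine samples at two visits that are 2 days (+/- 1 day) apart". The control-group list in Section 6.2 also names both groups and ends with "Visit 2: this should 2 days (+/- 1 day) after Visit 1".

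**Volumes.** Table 4 in Section 7 has one pooled control column, with 3 routine, 2 serum and 2 EDTA draws. Its row "Total blood volume" shows 55 mL, and its urine total is 110 mL. Total Blood Loss repeats that "approximately 55 ml whole blood will be drawn in control subjects (healthy volunteers and cancer control patients".

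**EDTA timing.** A sentence in Section 7 restricts the EDTA sample to baseline and Day 7. That fits the cisplatin schedule and neither control schedule.

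Neither amendment in Appendix 1 concerns control visits, so the protocol does not show which version is intended.

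**The concern.** Whether healthy controls attend at 14 to 28 days depends on which part of the protocol a site follows. Two things are at stake.

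- **Data.** Section 2.1 asks for within- and between-subject baseline variability. Section 9.2.1 compares biomarker profiles over time between the cisplatin cohort and both control cohorts. Cisplatin patients are sampled to Day 21 (+/- 7 days). A site that follows the text collects no control biomarker sample over that span, and a missed visit cannot be recovered later. If sites differ in which part they follow, Visit 3 data will be incomplete by site.
- **Disclosure.** A site that follows the table draws more blood from untreated healthy volunteers than the protocol states. Under Section 11.2 the protocol is the document that goes to ethics review.

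**Working it through.** **Formula.** Total volume = sum over sample types of (volume per sample x number of visits sampled). Volumes per sample are 5 mL (routine blood), 10 mL (serum), 10 mL (EDTA), 10 mL (routine urine) and 40 mL (biomarker urine), from Tables 1 to 3 of Section 3 and Table 4 of Section 7.

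**Step 1: reproduce the stated figures from Table 4.**

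| Group | Blood | Urine |
|---|---|---|
| Cisplatin | 9x5 + 8x10 + 2x10 = 145 mL | 9x10 + 8x40 = 410 mL |
| Controls (pooled) | 3x5 + 2x10 + 2x10 = 55 mL | 3x10 + 2x40 = 110 mL |

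All four totals reproduce, including the cisplatin statement "Approximately 145 mL whole blood will be drawn in patients receiving cisplatin treatment". The pooled control counts equal those of the cancer-control schedule (Table 2).

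**Step 2: apply the same formula to the healthy-control schedule (Table 3).** Routine samples are marked at Screening and Visits 1, 2 and 3 (4 times). Serum, EDTA and biomarker urine are marked at Visits 1, 2 and 3 (3 times each).

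- Blood: 4x5 + 3x10 + 3x10 = 80 mL. Excess over 55 mL: 25 mL, and 25/55 = 45%.
- Urine: 4x10 + 3x40 = 160 mL. Excess over 110 mL: 50 mL, and 50/110 = 45%.

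**Step 3: Screening and Visit 1 combined, with one routine sample serving both.**

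- Blood: 3x5 + 3x10 + 3x10 = 75 mL. Excess: 20 mL, and 20/55 = 36%.
- Urine: 3x10 + 3x40 = 150 mL. Excess: 40 mL, and 40/110 = 36%.

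On the same combined basis cancer controls need 2x5 + 2x10 + 2x10 = 50 mL. Visit 3 therefore adds 5 + 10 + 10 = 25 mL blood either way.

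**Step 4: can the EDTA sentence rescue 55 mL with Visit 3 kept?** The figures in brackets are for Screening and Visit 1 combined.

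- No EDTA at Visit 3: 4x5 + 3x10 + 2x10 = 70 mL (65 mL).
- EDTA at baseline only: 4x5 + 3x10 + 1x10 = 60 mL (55 mL).

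Only the last combination reaches 55 mL. It contradicts the EDTA marks in Table 3 and also Table 4, whose row "DIKI EDTA blood" counts two control draws.

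**Step 5: time coverage.** Control Visit 2 falls 2 +/- 1 days after Visit 1, so at most 3 days. The late cisplatin windows are 14 +/- 3 = 11 to 17 days and 21 +/- 7 = 14 to 28 days. Visit 3, at 14 to 28 days, is the only control sampling that overlaps them. With the planned 20 healthy controls, at most 20 control sample sets exist in that span under the table, and none under the text.

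**The case against.** The strongest reply is that nothing is miscalculated. Table 4 is correct for two visits. The design text, Section 6.2, Table 4 and Total Blood Loss all agree on two, and the healthy-control schedule stands alone. This stands: a reader might infer that 55 mL is an arithmetic error, but it is wrong only relative to the healthy-control schedule, and the protocol does not show which version was meant. The fault is the contradiction, and the volumes follow from how it is resolved. The word approximately does not bridge it, because 20 to 25 mL is the effect of a whole visit.

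Three other readings go further than the protocol supports.

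- *Visit 3 is needed to interpret the late cisplatin samples.* This is a reasonable inference from the windows, but the protocol gives Visit 3 no purpose and sets no 2 to 4 week interval for baseline variability. Cancer controls have no late sample in any part of the protocol, and the comparison is described as exploratory. What remains is that the planned comparison over time would lose its only late control data.
- *Sites will skip the visit.* A site working from the schedule table would not. The risk is inconsistency between sites.
- *Volunteers were told the wrong volume.* The information sheet was not available for review and may already match the table.

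It is also fair that the gap is small in absolute terms (80 mL is below the 145 mL for cisplatin patients) and that cisplatin sampling and kidney-injury classification are untouched.

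**Conclusion.** The contradiction is real, and no amendment explains it. If the healthy-control schedule applies, blood is understated by 25 mL (80 against 55 mL, 45%) and urine by 50 mL (160 against 110 mL, 45%). With Screening and Visit 1 combined the gaps are 20 mL and 40 mL (36%). If the two-visit text applies, 55 mL and 110 mL stand, and no control biomarker samples exist later than about 3 days after Visit 1.

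The 80 mL figure assumes every mark in the schedule is carried out, with a separate routine draw at Screening. The count of at most 20 late control sample sets assumes full enrolment and attendance, whereas Section 9.1 allows cohort sizes to change.

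Severity: should-fix. The protocol is wrong as written on whether a visit occurs, but the repair is wording and the affected analysis is exploratory.

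**What to change.** Decide whether Visit 3 is intended, then reconcile the Section 3 text, the healthy-control schedule, Section 6.2 and Section 7 (EDTA sentence, Table 4, Total Blood Loss).

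- **If Visit 3 is intended:** add it, for healthy controls only, to the Section 3 text and Section 6.2. Split the control column of Table 4 into cancer controls (55 mL blood, 110 mL urine) and healthy controls (up to 80 mL and 160 mL, or 75 mL and 150 mL with Screening and Visit 1 combined). Correct Total Blood Loss to match.
- **If Visit 3 is not intended:** delete it from the healthy-control schedule and state that no control biomarker data exist beyond about 3 days after Visit 1. The volumes can then stay.
- **In both cases:** limit the Section 7 sentence on EDTA timing to the cisplatin group, or align it with the control schedules, since it also conflicts with the EDTA draw at control Visit 2. Check that the volunteer information sheet agrees on visits and volumes, and change it only if it does not.

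The cost is amendment wording, its ethics submission under Section 11.2 and possibly a revised information sheet. No visit is added beyond those already in the schedule tables.

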### Sample Handling Procedures

Details on blood and urine sample handling and storage at the site as well as shipment conditions for frozen samples are detailed in a separate sample handling SOP.

## **8. ADVERSE EVENT REPORTING**

### **8.1 Definition of Adverse Events**

An Adverse Event (AE) is any untoward medical occurrence in a subject or clinical investigation subject administered a pharmaceutical product and which does not necessarily have to have a causal relationship with the intervention. An AE can therefore be any unfavourable and unintended sign (including an abnormal laboratory finding, for example), symptom, or disease temporally associated with the use of a pharmaceutical product, whether or not considered related to the study. Pre-existing conditions that worsen during a study are to be reported as AEs.

### **8.2 Reporting Period**

All clinical adverse events (AEs) encountered during the clinical study will be recorded on AE source documents and retained at the Investigator site.

### **8.3 Serious Adverse Events**

A serious adverse event (SAE) is any experience that suggests a significant hazard, contraindication, side effect or precaution. An SAE must fulfill at least one of the following criteria:

- is fatal (results in the outcome death)
- is life-threatening
- required in-patient hospitalization or prolongation of existing hospitalization
- results in persistent or significant disability/incapacity
- is a congenital anomaly/birth defect
- is medically significant or requires intervention to prevent one or other of the outcomes listed above

Serious Adverse Events unrelated to the study procedure and /or underlying conditions, must be collected and reported during the study and up to 15 days after the last visit.

### **8.4 Severity Assessment**

All clinical adverse events (AEs) encountered during the clinical study will be recorded on AE source documents and retained at the Investigator site. Intensity of AEs will be graded on a four-point scale (mild, moderate, severe and life threatening). A description of scales can be found below.

- Mild discomfort noticed but no disruption of normal daily activity
- Moderate discomfort sufficient to reduce or affect daily activity
- Severe inability to work or perform normal daily activity
- Life Threatening represents an immediate threat to life

Relationship of the AE to the study procedure or prescribed medications should also be assessed. Details can be found below.

### **8.5 Causality Assessment**

Relationship of the AE to the study procedure or prescribed medications should be assessed as probable, possible, remote or unlikely.

**PROBABLE (must have first three)**

This category applies to those AEs that are considered, with a high degree of certainty, to be related to the study procedures. An AE may be considered probable, if:

1. It follows a reasonable temporal sequence of the study procedures.
2. It cannot be reasonably explained by the known characteristics of the subject's clinical state, environmental or toxic factors, or other modes of therapy administered to the subject.
3. It disappears or decreases on cessation or reduction of the study procedures.
4. It follows a known pattern of response to the suspected study procedure.
5. It reappears upon rechallenge.

**POSSIBLE (must have first two)**

This category applies to those AEs in which the connection with the study procedures appears unlikely but cannot be ruled out with certainty. An AE may be considered possible if, or when:

1. It follows a reasonable temporal sequence of the study procedures.
2. It may have been produced by the subject's clinical state, environmental or toxic factors, or other modes of therapy administered to the subject.
3. It follows a known pattern of response to the suspected study procedure.

**REMOTE (must have first two)**

In general, this category is applicable to an AE that meets the following criteria:

1. It does not follow a reasonable temporal sequence of the study procedures.
2. It may readily have been produced by the subject's clinical state, environmental or toxic factors, or other modes of therapy administered to the subject.
3. It does not follow a known pattern of response to the suspected study procedure.
4. It does not reappear or worsen when the study procedure continues.

**UNRELATED**

This category is applicable to those AEs which are judged to be clearly and incontrovertibly due only to extraneous causes (disease, environment etc.) and do not meet the criteria for study procedures relationship listed under remote, possible or probable.

**8.6 Reporting Requirements****8.6.1 Serious Adverse Event Reporting Requirements**

Any adverse event (AE) that is serious, occurring during the course of the study, irrespective of the assessments performed on the subject, must be reported to the sponsor within one working day of its occurrence allowing expedited reporting.

The study will adhere to the full requirements of ICH Guidelines for Clinical Safety Data Management, Definitions and Standards for Expedited Reporting, Topic E2 will be adhered to. Complete information can be found in [Appendix xxx].

### **8.6.2 Non-Serious Adverse Event Reporting Requirements**

As this is a non-therapeutic study, all AEs reported will be retained at the Investigator site as source notes.

## **9. DATA ANALYSIS/STATISTICAL METHODS**

### **9.1 Sample Size**

The maximum sample size for this multiple cohort observational study is 140 patient/subjects comprising;

- 100 patients in the cisplatin cohort to have a minimum of 20 subjects who show post-cisplatin BUN and serum creatinine changes that qualify as AKI.
- 20 patients in the patient control cohort.
- 20 subjects in the volunteer control cohort.

A sample size of 100 patients in the cisplatin cohort and 20 patients/subjects in each control cohort will enable a reliable assessment of the form of the statistical distribution for baseline values for each novel BM. In addition, a sample size of 20 cisplatin patients with AKI and 20 patients/subjects in each control cohort will enable an exploratory comparison between cohorts to detect patterns of difference in the BM profiles over time.

The sample size of the cisplatin-treated and the control cohorts may be adjusted during the course of the study based on interim analyses of novel biomarker patterns as well as the incidence of AKI as defined by BUN and serum creatinine changes in the cisplatin cohort.

### **9.2 Statistical Analysis**

#### **9.2.1 Analysis of Primary Endpoint**

The full list of novel serum and urinary biomarkers (BM) included in the analysis are provided in Table 3 (Section 7).

The statistical distribution of the baseline BM values will be described graphically and by calculating the mean, median, standard deviation, inter-quartile range and range within each cohort and overall. The form of the relationships between each pair of BMs will also be investigated.

For each BM, the profile of values over time will be summarised and inspected to see if any patterns of change differ between the cisplatin cohort and the two control cohorts. BMs that show a different response between cohorts will be further investigated to characterise the form of the response and to evaluate if the response appears associated with concurrent changes in serum creatinine and BUN.

BMs will be assessed, one at a time, for their ability to predict DIKI as defined by the AKIN and RIFLE criteria[refs]. In addition, each patient in the cisplatin cohort will be reviewed by an adjudication panel to assess presence of DIKI using all of the available data. BMs will also be assessed for their ability to predict DIKI as defined by the adjudication panel. Exploratory ROC curves will be generated and estimates of sensitivity and specificity will be given. BMs will be ranked according to their estimated probability of having a sensitivity and specificity of greater than 80% for predicting DIKI.

Exploratory analyses may also be conducted to evaluate the potential for combining BMs to enhance prediction of DIKI.

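### Section 9.1 supports the biomarker profile comparison with the AKI patients, but 9.2.1 and 9.2.2 describe it only for the whole cisplatin cohort; profiles by injury status should be added

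*Protocol*

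**What the plan says.** Protocol 9.1 sets the cisplatin cohort at "100 patients in the cisplatin cohort to have a minimum of 20 subjects who show post-cisplatin BUN and serum creatinine changes that qualify as AKI", with "20 patients in the patient control cohort" and "20 subjects in the volunteer control cohort". It then says that "a sample size of 20 cisplatin patients with AKI and 20 patients/subjects in each control cohort will enable an exploratory comparison between cohorts", the purpose being to detect differences in biomarker profiles over time.

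Protocol 9.2.1 says that the profile of each biomarker will be summarised and "inspected to see if any patterns of change differ between the cisplatin cohort and the two control cohorts". Section 9.2.2 uses the same wording for BUN and creatinine. Section 9.2.1 continues: "BMs that show a different response between cohorts will be further investigated to characterise the form of the response". For those biomarkers it adds a check on whether the response goes along with simultaneous creatinine and BUN changes.

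A separate paragraph of 9.2.1 says: "BMs will be assessed, one at a time, for their ability to predict DIKI as defined by the AKIN and RIFLE criteria". The same is planned against the adjudication panel's classification, with ROC curves and a ranking on the probability that sensitivity and specificity both exceed 80%.

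**The concern.** The two sections fix different groups for the same analysis. In 9.1 the cisplatin side of the profile comparison is the AKI subgroup. In 9.2.1 and 9.2.2 it is the whole cohort, in which up to 80 of 100 patients have no AKI at the planned minimum. Section 9.2 describes no profile summary by AKI or DIKI status.

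This matters because the inspection decides which biomarkers have the form of their response studied, and Section 2.1 uses the pattern and time-course data to choose candidates and sampling times for confirmatory studies. Averaging over the whole cohort can flatten the profile of a marker that rises mainly in injured patients. Conversely, a marker that moves in every treated patient for reasons other than injury would look different from controls.

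**Working it through.** **Inputs from the protocol.** Cisplatin cohort 100, at least 20 with AKI (9.1), so the AKI share is p = 20/100 = 0.20 at the minimum. Controls: 20 per cohort (9.1). Nephrotoxicity in about one third of high-dose patients (1.1), i.e. about 33 of 100. Section 9.1 gives no alpha, power, effect size or SD, so there is no power figure to reproduce.

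**Assumptions.** Normal change scores at one common time-point, SD 1 within each group; AKI patients shifted by d = 1 SD; non-AKI patients shifted by a fraction f of that; one control cohort of 20; two-sided 5%. The protocol plans inspection and no test, so the power figures are only a yardstick.

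**Step 1: dilution of the mean difference** = 1 / (p + (1 − p)f).
- p = 0.20, f = 0: 1/0.20 = 5.0
- p = 1/3, f = 0: 3.0
- p = 0.20, f = 0.25: 1/0.40 = 2.5
- p = 0.20, f = 0.5: 1/0.60 = 1.67
- p = 0.20, f = 0.75: 1/0.80 = 1.25

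**Step 2: yardstick with no response in non-AKI patients.** Power is Φ(z − 1.96).
- AKI versus controls, 20 v 20: z = 1/√(1/20 + 1/20) = 3.16, power 88.5%.
- Whole cohort versus controls, 100 v 20: mean 0.20, variance 1 + p(1 − p)d² = 1.16, z = 0.20/√(1.16/100 + 1/20) = 0.81, power 12.4%.
- With 33 AKI cases: AKI versus controls z = 1/√(1/33 + 1/20) = 3.53, power 94%; whole cohort z = 0.33/√(1.221/100 + 1/20) = 1.32, power 26%.

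At 20 AKI cases z falls about 3.9-fold (3.16/0.81), less than five-fold, because the larger group offsets part of the dilution.

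**Step 3: partial response in non-AKI patients**, 20 AKI of 100. Whole cohort: mean 0.2 + 0.8f, variance 1 + 0.16(1 − f)². AKI versus non-AKI: z = (1 − f)/√(1/20 + 1/80) = 4(1 − f).

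| f | AKI v controls | Whole cohort v controls | AKI v non-AKI |
|---|---|---|---|
| 0 | 88% | 12% | 98% |
| 0.25 | 88% | 37% | 85% |
| 0.5 | 88% | 68% | 52% |
| 0.75 | 88% | 90% | 17% |

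A Welch t-test simulation (20,000 replicates) gives the same pattern, up to about 3.5 percentage points lower.

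**Step 4: exposure without injury.** A shift s in all 100 cisplatin patients, unrelated to AKI, gives z = s/√(1/100 + 1/20) against 20 controls. For s = 0.5, z = 2.04 and power is 53%; for s = 0.8, z = 3.27 and power is 90%. The AKI versus non-AKI contrast stays at 5%.

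**The case against.** The strongest reply is that injury is already addressed in the same section. A reader might infer that the plan selects markers on cisplatin exposure instead of kidney injury. The text does not support that. Section 9.2.1 goes on to relate a differing response to creatinine and BUN. It then assesses biomarkers one at a time against DIKI and ranks them on that, with no stated restriction to those that passed the inspection. An exposure-only marker would be looked at more closely and should then rank low. Section 2.2 also sets maximum change, time to maximum and the other summaries for every biomarker. All of this stands, and it limits the point. It does not supply profiles by injury status, which neither ROC curves nor the 2.2 summaries provide as written.

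A reader might also take five-fold dilution as the expected loss. It needs exactly 20% AKI, although 9.1 calls 20 a minimum, and no response at all in non-AKI patients. Section 1.1 argues against the latter: creatinine and BUN may miss substantial loss of function, which is why more sensitive markers are sought.

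For the same reason, replacing the cohort comparison by DIKI versus no DIKI would be a mistake. In step 3 that contrast falls from 98% to 52% when non-AKI patients show half the response, so it penalises markers of milder injury.

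Finally, 9.1 and 9.2.1 could be read as complementary, with subgroup displays left to the SAP. But the protocol itself names the groups in both places, and they differ.

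**Conclusion.** The point holds as a mismatch between 9.1 and 9.2.1/9.2.2 in who is compared in the profile step. The whole-cohort contrast can hide the profile of a marker that rises mainly in injured patients, and by itself it cannot separate exposure from injury. The size depends on two things the protocol does not fix: the AKI share, and how far non-AKI patients respond. On the yardstick, a marker raised 1 SD in AKI patients only would be seen about 12% of the time instead of 88% at 20 AKI cases, and 26% instead of 94% at 33. The gap closes once non-AKI patients show about 75% of the AKI response. The consequence is limited to profile and time-course characterisation; the documents give no ground for saying that the DIKI ranking is affected. It is an inexpensive improvement to an exploratory plan.

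**What to change.** In 9.2.1 and 9.2.2:
- Keep the comparison of the whole cisplatin cohort with controls, and add profiles for cisplatin patients with DIKI and without DIKI, shown beside the two control cohorts. Say which of the planned DIKI classifications defines the groups.
- Take a biomarker forward for characterisation if it differs in any of these: whole cisplatin cohort versus controls, DIKI versus controls (the comparison in 9.1), or DIKI versus no DIKI. Do not make DIKI versus no DIKI the sole criterion.
- Report no DIKI versus controls separately, as an effect of exposure or of subclinical injury.
- State that the DIKI-prediction step covers all biomarkers, whatever the inspection shows.

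The cost is wording and one grouping variable. DIKI classification of the cisplatin cohort is already planned, so no patients, samples or assays are added. The profile summaries must wait for that classification, and slightly more biomarkers may be taken forward.
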